#### • Feasibility and logistics

To determine the feasibility of the intervention and logistics of the procedure, the following information will be recorded using a datasheet which will include a post-treatment survey: time it takes to explain the procedure, equipment, visuals, etc. to the participant; time it takes the participant to familiarize himself with the equipment; time it takes to set-up the equipment; time it takes to administer the exposure session; any adverse effects due to intervention; ease of using the equipment; subject's acceptability and opinions/thoughts of using the equipment.

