### Description of the overall project

The proposed project will consist of two interlinked experimental studies: Study 1 and Study 2.

**Study 1 **will incorporate an observational within-subject study design and aims to ascertain the neurophysiological changes occurring in the functional brain areas associated with pain catastrophizing when catastrophizing FMS patients are exposed to various visuals of exercise activities. Functional magnetic resonance imaging (fMRI) will be used to observe these neurophysiological changes within the associated functional brain areas. Study 1 will be conducted at the Cape Universities Brain Imaging Centre (CUBIC) situated at the Stellenbosch University's Tygerberg medical campus in Cape Town, South Africa (SA).

**Study 2 **will incorporate a quasi-, within-subject/between-groups experimental (pre- and post-, with/without treatment) study design and aims to ascertain the preliminary efficacy of visual exposure to exercise activities on pain catastrophizing in FMS patients. Clinical improvement in pain catastrophizing will be measured using objective and subjective outcome measures. The feasibility of using visual exposure to exercise activities as a treatment for pain catastrophization experienced by FMS patients in terms of: 1) time taken to administer; 2) ease of use; 3) safety of administration; 4) participant acceptability; and 5) participant opinion/thoughts of the intervention, will also be ascertained. Study 2 will be conducted at the Body in Motion analysis lab at the Stellenbosch University's Tygerberg medical campus in Cape Town, SA.

It is envisaged that the data collection period of the project will commence in June/July 2011 and be completed by September/October 2011.

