
***Study 2: ***On completing baseline scans in study 1, group B subjects (n = 10) will be instructed to complete another set of the PCS and TSK and continue daily activities as normal for the next eight weeks (control group). No other education/treatment/information will be given to group B subjects. Appointments to return to CUBIC for final scans after eight weeks will be scheduled for group B subjects. On completing baseline scans in study 1, one-hour long sessions will be scheduled for group A subjects (n = 10) twice a week for eight weeks (intervention group). During the twice weekly treatment sessions, subjects will be placed in an isolated room and be exposed to visuals of various exercise activities. Visual exposure to exercise activities will be delivered via a VR head-mount display (HMD); namely the eMagin Z800 3DVISOR linked to an ASUS K61IC series laptop. The eMagin Z800 3DVISOR has a highly sophisticated built-in head tracker which allows the user six degrees of freedom in motion [28]. The HMD is placed on the head of the user, blocking off the surrounding environment. The visuals relayed to the HMD via a connected laptop are viewed on two 3D OLED 0.59 inch micro displays, which to the user seem to play as huge as a 105-inch screen. These specific features of the eMagin Z800 3DVISOR enhance the immersion of the user into the virtual environment [28]. Software will consist of an hour-long DVD comprised of various simulated exercise activities. The subject may only be accompanied by a research assistant or translator. The PCS and TSK will be administered before and after each session. Information relating to the feasibility and logistics of the study will be collected from Group A's subjects at the end of the eight-week treatment program.

The PCS and TSK will be administered before and after the eight week time period for both groups. No PCS and TSK scores will be collected during the eight weeks for group B's subjects. At the end of the eight-week study period, both groups will undergo final fMRI scans.

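### The safety item records only effects already attributed to the intervention, and only in Group A, so the count has no untreated background rate to be read against

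*Protocol article*

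**What the plan says.** Under Description of the overall project, Study 2 is to establish the feasibility of the visual exposure on five criteria, including "3) safety of administration; 4) participant acceptability".

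Under Feasibility and logistics, "the following information will be recorded using a datasheet which will include a post-treatment survey". The list that follows is mostly about timing and ease of use. Its one safety entry is "any adverse effects due to intervention". No rule or assessor for that attribution is given.

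Under Study procedures (Study 2), "Information relating to the feasibility and logistics of the study will be collected from Group A's subjects at the end of the eight-week treatment program". Group A has 10 subjects treated twice weekly for eight weeks. Group B has 10 subjects on a waiting list. For Group B the stated Study 2 data are the PCS, the TSK and the fMRI scans.

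Three other passages bear on the point:

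- Loss to follow-up requires the reasons for ending or pausing treatment to be documented.
- Allocation to study groups states the FIQR only for the start of Study 1.
- Statistical analysis plans between-group comparison of questionnaire scores for the PCS and TSK, and states none for adverse effects.

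**The concern.** Fibromyalgia brings pain and fatigue whether or not a patient is wearing a headset. Over eight weeks some Group A subjects can be expected to report new or worse symptoms that VRET did not cause. The datasheet item asks for a judgement of cause before the event is recorded, so the count reflects both what happened and how readily it was blamed on the intervention.

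The error can run either way. Background symptoms may be booked to VRET, or genuine effects of the headset or visuals may be put down to the disease and left out.

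A randomised untreated group could show the background rate. It is followed over the same eight weeks and is already seen at both ends, but the text does not use it for this purpose. At stake is how one declared feasibility aim can be interpreted.

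**Working it through.** The article states no safety figure, adverse-effect rate or sample-size calculation, so there is nothing to reproduce. The check has three parts.

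**1. The passages side by side**

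| Question | What the article states |
|---|---|
| Is safety an aim? | Yes, as one of five feasibility criteria |
| What is recorded? | Effects attributed to the intervention |
| From whom? | Group A (n = 10) |
| Any unfiltered record? | Reasons for stopping or pausing treatment, in treated subjects only |
| Any later fibromyalgia symptom measure in either arm? | None stated; FIQR at the start of Study 1 only |
| When is Group B seen? | Baseline, and week 8 for PCS, TSK and fMRI |

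**2. How far attribution can move the count**

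Let *b* be the share of subjects with a new or worse symptom unrelated to VRET over eight weeks, and *m* the share of these attributed to VRET. With no true VRET effect, the recorded rate is *b* × *m*. Both inputs are assumptions.

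| Assumed *b* | *m* = 0 | *m* = 0.25 | *m* = 0.50 | *m* = 1 |
|---|---|---|---|---|
| 20% | 0% | 5% | 10% | 20% |
| 50% | 0% | 12.5% | 25% | 50% |
| 80% | 0% | 20% | 40% | 80% |

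At *b* = 50%, the expected count among 10 subjects runs from 10 × 0.50 × 0 = 0 to 10 × 0.50 × 1 = 5. Nothing in the planned data fixes where in that range an observed count falls.

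A count of zero is also weak. With 0 of 10, the one-sided 95% upper bound is 1 − 0.05^(1/10) = 0.259, about 26%. That bound applies only if every event was eligible to be recorded.

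**3. What recording in both arms would give**

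The Fisher exact test, 10 v 10, two-sided 0.05, with assumed Group B v Group A rates:

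| Group B v Group A | Power |
|---|---|
| 10% v 30% | 6% |
| 10% v 50% | 30% |
| 30% v 60% | 12% |
| 50% v 80% | 13% |
| 20% v 70% | 43% |

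This is no basis for a test. The Group B count still changes how a Group A count reads. With 6 of 10 in Group A:

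- If Group B has 5 of 10, the difference is 10 points (Newcombe 95% interval −29 to +45).
- If Group B has 1 of 10, the difference is 50 points (+8 to +75).

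**The case against.** The best defence is that the aim is narrow. Safety sits beside time, ease of use and acceptability, and concerns administering the exposure. Group B receives no exposure, no comparative safety hypothesis is stated, and a condensed article may leave adverse-event procedures to a fuller protocol. This stands to the extent that the plan does not contradict itself and missing detail on procedure is no fault. It does not remove the point, because the two restrictions, attributed effects only and Group A only, are stated on the page.

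A reader might go further in four ways that the text does not support:

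- *That VRET effects cannot be separated from fibromyalgia symptoms at all.* Reasons for stopping or pausing carry no attribution filter. PCS and TSK are taken around every Group A session, although they measure catastrophizing and fear, not general symptoms. The datasheet also holds items such as set-up and session time, so it need not be purely an end-of-study recall form.
- *That unblinded staff or the subject decide attribution.* No assessor is named.
- *That Group A would show the full background rate, for example 5 of 10 at 50%, with no VRET effect.* That needs every background symptom to be attributed to VRET. It is the top of the range.
- *That a Group B count would let the background be subtracted cleanly.* The intervals above show otherwise. Group A also has 2 × 8 = 16 sessions with staff, so symptoms will be noticed more often there.

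Reactions to the scans are a separate matter: fMRI is the measurement, not the treatment whose feasibility is asked about.

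**Conclusion.** The point holds as a minor one. As written, the safety count is filtered by a judgement of cause before recording and has no untreated comparator, although the control group is already seen at baseline and week 8. With an assumed 50% background rate and no VRET effect, the recorded rate could be anything from 0% to 50%. At 20% and 80% background, the upper ends are 20% and 80%. These rates are illustrations, since the documents supply none. The conclusion itself rests on the stated wording and on the premise that these patients have symptoms without VRET. It concerns the interpretation of one feasibility criterion, and efficacy is not affected.

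**What to change.** Under Feasibility and logistics, replace the adverse-effect entry with: *any new or worsened symptom, regardless of suspected cause; relationship to the intervention recorded separately*. Then:

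1. In Group A, note such symptoms at each session as well.
2. Ask both groups the same short fixed symptom list at the existing baseline and week-8 visits.
3. Report counts by arm with exact intervals, and state that 10 v 10 is not a powered safety comparison.
4. Base the arm comparison only on the common baseline and week-8 list, because Group A has more staff contact. Report the session records for Group A alone.

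The cost is a short addition to the datasheet and a few minutes at visits already planned, with no new visits or staff. More events will be listed, so the record may look less favourable. The week-8 list relies on recall and may miss brief symptoms, which is why the session notes in Group A are worth keeping.

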#### • Loss to follow-up

Should subjects not be able to handle being exposed to the visual of the exercise activities, he/she will be allowed to stop the exposure therapy treatment and carry on at a later stage. Should the subject refuse to participate any longer, data will be retained regardless as to how many sessions were completed and analyzed accordingly. All reasons for termination or suspension of treatments will be documented.

### Data collection and storage

The research assistant will document the randomized order of the stimuli/'off' periods during each run for each subject on a simple datasheet. This information will be blinded from the rest of the research team. Neurophysiological changes occurring during the fMRI sequence will be recorded and standard MEMPRAGE and EPI BOLD sequences will be acquired. fMRI data for each subject will be saved and stored on two hard-drives, under the reference number allocated to that subject. A research assistant will administer and collect completed PCS, TSK, GPPAQ and FIQR questionnaires, as well as sociodemographic forms from subjects. Data collected will be stored in the subject's respective folders. Back-up files of all data will be made and stored in a separate location. Folders, data and back-up data will be stored in a locked room with controlled access at all times. All subject identification and information will be kept confidential.

### Statistical analysis

***Study 1: ***fMRI data acquired from the subjects will be analyzed by a blinded radiologist or physiologist. The principle researcher will be involved in the analysis of the data. Contrasts between the different sets of data will be analyzed using Oxford's FMRIB Software Library (FSL), which is currently available at CUBIC. FSL is a collection of functional and structural brain image analysis tools, written by members of the Image Analysis Group at the Oxford Centre for Functional Magnetic Resonance Imaging of the Brain (FMRIB), Oxford University. FSL is distributed as freeware and most of the tools can be run both from the unix command line and as a graphical user interface [29]. Single-subject analyses will be performed by linear regression of the fMRI data. The functional brain regions to be analyzed and compared will include the areas previously associated with pain catastrophizing namely: the secondary somatosensory cortex (SII), contralateral insula, primary somatosensory cortex (SI), inferior parietal lobule and thalamus, contralateral anterior ACC, the contralateral and ipsilateral lentiform activation in SI, anterior and posterior cerebellum, posterior cingulate gyrus, and superior and inferior frontal gyrus [30]. The scans will be registered to high resolution Montreal Neurological Institute (MNI) structural scans so that the FSL grey matter atlas tools can be used to correctly locate the regions of interest.

***Study 2: ***Mean pre- and post-session (intervention group), as well as mean pre- and post-treatment (intervention and control group) PCS and TSK scores will be analyzed and compared between the groups and within-subjects for preliminary efficacy of the intervention. Paired *t test *for comparison of two dependent samples and contrast for the significance of the Pearson r correlation between two quantitative variables will be assessed. The open-ended questions of the post-treatment survey will be qualitatively analyzed and the closed-ended questions will be quantitatively analyzed using frequency counts. Post-intervention fMRI data will be analyzed and compared to subject fMRI data obtained at baseline. Single-subject analyses will be performed by linear regression of the fMRI data.

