### Study population and recruitment process

Twenty eligible subjects will be conveniently sampled from the available FMS population currently registered at the Tygerberg Hospital (TBH) Rheumatology clinic and/or attending the monthly FMS group meetings held at the TBH Occupational therapy (OT) department. The rheumatologists and/or occupational therapist working in the TBH Rheumatology clinic and/or OT department will be asked to identify all new or previously diagnosed FMS patients attending the clinic. The principle researcher and research assistant(s) will approach all potential patients personally or telephonically, and invite them to participate in the study. In addition, the clinic's patient database will be manually searched for all potential patients who have been diagnosed with FMS, but no longer attend the monthly meetings or the clinic. All potential patients listed on the database for whom contact details are available will be contacted telephonically and invited to participate in this project.

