### Subject inclusion and exclusion criteria

Adult male and female subjects aged 18 years and older, who have been clinically diagnosed with FMS according to the American College Rheumatology (ACR) criteria [24] by a qualified rheumatologist; subjectively display high PCS (more than 24 points) and TSK (more than 37 points) scores, and are registered as a patient at TBH Rheumatology clinic/OT department, will be included in this study. Subjects diagnosed with other conditions not related to FMS i.e. cancer; who have severe physical disabilities; who suffer from chronic rheumatoid conditions i.e. systemic lupus erythmatosus and rheumatoid arthritis; who have previously been hospitalized for a major psychiatric disorder; who have an uncontrolled endocrine or allergic disorder; who are using medication other than the prescribed pharmacologic agents for FMS symptoms; who have been using any narcotics long-term; who currently or who have previously abused any illicit substances or alcohol; have been diagnosed with epilepsy, or other conditions contraindicated in the use of visual exposures to stimuli; who display any contraindications which prohibit the use of fMRI, i.e. cardiac pacemakers, metal implants, claustrophobia, pregnancy and cochlear implants; and who are unable to discontinue intake of anti-depressants 4 weeks prior to commencement of study, will be excluded from this study.

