### Allocation to study groups

On consenting to participate in this project, subjects will be randomly allocated into Group A (VRET/intervention group) or Group B ("waiting list"/control group) using a computer-generated random number sequence constructed by an independent statistician. Allocation will be concealed in opaque envelopes containing the letters 'A' or 'B' and administered by an independent individual not part of the study. Study procedures will be thoroughly explained to each subject. Sociodemographic forms, the General Practice Physical Activity Questionnaire (GPPAQ), and the Revised Fibromyalgia Impact Questionnaire (FIQR) will be administered to each subject at the beginning of study 1. *GPPAQ is a validated screening tool for use in primary care to assess adult (16 - 74 years) physical activity levels *[25]. *It provides a simple 4-level physical activity index, categorizing patients as inactive, moderately inactive, moderately active and active. The FIQR is an updated version of the Fibromyalgia Impact Questionnaire (FIQ) that has good psychometric properties, can be completed in less than 2 minutes and is easy to score. It has scoring characteristics comparable to the original FIQ, making it possible to compare past FIQR results with future FIQR results *[26]. *The FIQR assesses level of functioning. The original FIQ was developed and validated by Burckhardt et al (1991) to assess the current health status of women with FMS *[27].

Study groups will progress as a cluster group from study 1 to study 2 to reduce the period of time between baseline scans and final post-intervention/control scans.

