## Discussion

The premise is if visuals of various exercise activities trigger the functional brain areas associated with pain catastrophizing in FMS subjects; then as a treatment, it can be postulated that graded and repeated exposure to visuals of exercise activities using a VRET program could possibly decrease pain catastrophizing and subsequently decrease fear to movement, essentially improving compliance towards exercise therapy programs among FMS patients. Proof-of-concept for the development and testing of a novel VRET program for exercise-related pain catastrophizing in FMS will either be established or negated. The results of this project are envisaged to revolutionize FMS and pain catastrophizing research and in the future, assist health professionals and FMS patients in reducing despondency regarding FMS management.

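### Study 2 promises a between-group comparison of PCS and TSK, but the only tests it names cannot compare the two randomised groups

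*Protocol article*

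**What the plan says.** Under Statistical analysis, Study 2, the protocol article states that "PCS and TSK scores will be analyzed and compared between the groups and within-subjects for preliminary efficacy of the intervention". The next sentence names the methods, a paired t test and a Pearson r; its wording is "for comparison of two dependent samples and contrast for the significance of the Pearson r correlation between two quantitative variables will be assessed". No two-sample test, ANCOVA, mixed model or group-by-time test appears. The fMRI method given for Study 2 is single-subject regression, with post-treatment scans compared with the same subject's baseline, so it names no group contrast either.

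The between-group contrast belongs to the design. Description of the overall project gives Study 2 a "within-subject/between-groups experimental (pre- and post-, with/without treatment) study design", and Allocation to study groups says "subjects will be randomly allocated into Group A (VRET/intervention group) or Group B". Study procedures gives 10 subjects per group.

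Two further statements bear on the point. Entry requires that subjects "subjectively display high PCS (more than 24 points) and TSK (more than 37 points) scores". Study procedures, Study 1, has a PCS and TSK set completed before the scan and used as baseline.

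**The concern.** A paired t test needs two measurements on the same units. Groups A and B are different people, so it can be used only inside each arm. A Pearson correlation between two quantitative variables does not estimate a group difference, because group is not a quantitative variable. The named methods therefore do not deliver the comparison promised one sentence earlier.

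An analyst who runs only what is named would ask whether A changed and, separately, whether B changed. A significant fall in A would then be open to a VRET reading, although passage of time, attention from twice-weekly sessions and repeated completion of the questionnaires could each produce it. Repeated testing is unequal by design: group A completes PCS and TSK before and after every session, and group B completes none during the eight weeks. The contrast that randomisation was set up to provide would go untested.

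**Working it through.** The article states no sample-size, power or alpha calculation, so there is no planned figure to reproduce. The checks are as follows.

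**1. Which comparison each named method can make**

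| Method named | What it compares | Tests A against B? |
|---|---|---|
| Paired t test, dependent samples | Pre with post inside one arm | No |
| Pearson r, two quantitative variables | Association of two scores | No, as described |
| Single-subject fMRI regression | A subject with own baseline | No |

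A Pearson r with group coded 0/1 would be equivalent to a two-sample t test, but the text limits r to two quantitative variables.

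**2. What a paired test in group A shows when VRET does nothing**

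Inputs: n = 10 in group A (Study procedures); two-sided 5% (assumed); an equal standardised within-subject change dz in both arms (assumed; the documents give no value).

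Under the alternative the paired t statistic is noncentral t with 9 df and noncentrality dz × √10. The critical value is t(0.975, 9) = 2.262. If both arms have the same chance p of significance and are independent, the chance that A is significant and B is not is p(1 − p).

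| dz (assumed) | dz × √10 | p, A significant | p(1 − p) |
|---|---|---|---|
| 0.5 | 1.58 | 0.293 | 0.207 |
| 0.7 | 2.21 | 0.506 | 0.250 |
| 0.9 | 2.85 | 0.717 | 0.203 |

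A simulation on the PCS scale points the same way (4,000 trials per setting; assumed SD 11, population mean 25, reliability 0.8, fresh baseline). With an equal non-specific fall of 2, 4 or 6 points in both arms, group A shows a significant fall in 13%, 37% or 68% of trials. A two-sample t test on change stays at about 5%.

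**3. How much the entry cut-offs contribute**

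Same simulation, with no change at all beyond selection on PCS above 24 (assumed SD 11, mean 20 to 30, reliability 0.7 to 0.9). The nominal rate for a significant fall in A is 2.5%.

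| Baseline used | Significant fall in A | Mean spurious fall |
|---|---|---|
| Eligibility score doubles as baseline | 4% to 22% | 0.4 to 3.4 points |
| Separate baseline, error correlation 0.5 | 4% to 9% | 0.2 to 1.7 points |
| Separate baseline, independent error | 2% to 3% | about 0 |

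The between-group test stays at 4% to 6% in every row.

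**4. Precision of the between-group estimate**

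ANCOVA 95% CI half-width = t(0.975, 17) × SD × √(1 − r²) × √(2/10). With SD 8 and pre-post correlation r = 0.6 (both assumed): 2.110 × 8 × 0.8 × 0.447 = 6.0 PCS points out of 52. Varying SD from 6 to 12 at r = 0.6 gives 4.5 to 9.1. Varying r from 0.3 to 0.8 as well gives about 3.4 to 10.8.

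The difference detectable with 80% power at 10 per group is 1.32 SD unadjusted, and 1.32 × 0.8 = 1.06 SD with ANCOVA at r = 0.6. Unadjusted power is 19%, 40% and 56% at a difference of 0.5, 0.8 and 1.0 SD.

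**The case against.** The strongest reply is that the between-group comparison is stated in plain words. The paired test can be read as serving the within-subject half of that sentence, and a condensed article may leave the other test to a fuller document. This stands in part: the article never says the paired test is the sole efficacy test, so the consequence is conditional on the named tests being the ones run. It does not remove the point. The article was not silent on tests; it chose two, and neither fits the first comparison it promised.

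Three stronger readings are tempting, and the documents do not support them.

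- A reader might infer that the fall in scores will be driven by selecting high scorers. The scan-day PCS and TSK set appears to be separate from the eligibility score. If its error is independent, selection adds almost nothing (third table row in step 3).
- A reader might take 29%, 51% and 72% as the trial's expected false-positive rates. They depend on the assumed dz. At SD 8 and r = 0.6, dz of 0.5 to 0.9 means 8 × √0.8 × dz, about 3.6 to 6.4 points. Even the lowest exceeds the largest selection-driven fall found (3.4 points, at SD 11).
- A reader might infer that a non-significant PCS test will be taken to disprove VRET, because the Discussion says proof-of-concept "will either be established or negated". That phrase covers the whole project, which also includes fMRI and feasibility data, and no text ties it to a PCS test.

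It is also fair that ANCOVA is not the only valid choice. A two-sample t test on change holds its error rate as well.

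**Conclusion.** The mismatch is real and sits within one section: a between-group comparison is promised, and the only methods named cannot make it for two independent groups of 10. If those methods are followed literally, the efficacy inference reduces to separate within-arm changes that cannot be attributed to VRET. The size depends on how much both arms would improve without any VRET effect, which the documents do not give. For assumed dz of 0.5 to 0.9, group A's paired test would be significant in about 29% to 72% of trials, against about 5% for a between-group test.

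Regression to the mean is a secondary concern. It matters mainly if the eligibility score doubles as baseline or its error is correlated with the baseline error. It would go too far to say that the control group contributes nothing, since the plan states the intention to use it.

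With 10 per group the between-group result will be imprecise (half-width about 6 PCS points, or 3.4 to 10.8 over the assumed ranges of SD and r). A non-significant difference should therefore not, on its own, count as negating proof-of-concept. Whether a given interval excludes a worthwhile effect cannot be judged here, because the article defines no such effect.

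**What to change.** Replace the Study 2 test sentence with wording such as: The efficacy analysis is the between-group difference in week-8 PCS from an ANCOVA with group and the pre-scan baseline PCS, reported with its 95% CI; TSK is analysed in the same way. Paired within-group changes and session-level changes are descriptive.

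Naming the pre-scan set matters because there are other candidates: Study procedures, Study 2, also has group B complete a further set after the scan, and group A complete sets before each session.

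Add that, with 10 per group, the result is reported as an estimate with its CI, and that a non-significant difference is not by itself read as negating proof-of-concept.

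Cost: a change of wording and one residual degree of freedom (17 instead of 18). No new data are needed, because pre- and post-treatment PCS and TSK are already collected in both groups.
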